### Study objectives and outcome measures

The overall objective of HeartMan is to improve disease management, resulting in an improvement in HRQoL after a 6 months intervention period.

Secondary objectives are the effects of HeartMan on behavioural outcomes, illness perception and clinical outcomes which may impact disease management and HRQoL. Additional secondary aims encompass the effects of psychological interventions within HeartMan and a user-friendly design of the HeartMan system.

Primary and secondary outcome measures, which are assessed in the intervention and control group, are listed below. These measures are collected at start and end of the study, unless otherwise stated.

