#### Secondary objectives

Effect of HeartMan on behavioural outcomes, which are:Adherence to dietary recommendations, measured by a self-composed questionnaire on nutritional knowledge and eating behaviourActivity behaviour, daily measured by the number of calories (via an accelerometer in the HeartMan wristband sensor)Medication adherence by questioning the patient on their medication intake on a weekly basisSexual activity, assessed with the Sexual Adjustment Scale [22] and Needs for Sexual Counselling Scale in chronic HF [23]Effect of HeartMan on illness perception, evaluated with the Brief Illness Perception Questionnaire [24]Effect of HeartMan on exercise tolerance, measured by:Change in resting heart rate and heart rate during exerciseDistance obtained at the six–minute walking test (6MWT) [25]Effect of psychological interventions in HeartMan – cognitive behavioural therapy and mindfulness exercises – on anxiety and depressive feelings, measured with State Trait Anxiety Inventory [26] and the Beck Depression Inventory II [27]Evaluation of the user experience of HeartMan to assess the expectations towards the system and the patient’s experiences (only measured in the intervention group), evaluated with the Unified Theory of Acceptance and Use of Technology questionnaire, [28] adapted to the objectives of the HeartMan system and to the population of elderly users [29]

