#### End-of-study visit

The intervention is terminated after using the system for three to six months. At this time, all participants from the intervention and control group undergo the end-of-study examination in the hospital that entails the same questionnaires and tests as during the baseline visit.

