#### Statistical analysis

The main analysis of primary and secondary endpoints will be based on the Intention-To-Treat principle, i.e. including all patients in the analysis who did not drop out within the first 4 weeks of the trial. In order to assess the clinical effect of the HeartMan intervention on the different outcomes, an additional per-protocol analysis will be performed in patients who adhere to the treatment plan for at least 50%. Based on these results, a dose-response analysis will be conducted to verify the relation between the level of adherence and intervention effects.

Prior to each analysis, distribution of the variables will be checked in order to choose correct statistical tests and identify outliers. In all analyses, *p* values < 0.05 will be considered to be statistically significant.

Effects of the proof-of-concept trial will be assessed by analysing baseline and end-of-investigation data between and among treatment groups. The primary endpoint of the HeartMan project is the self-reported improvement in HRQoL. First, T-tests or its non-parametric variant and chi-square tests will be used to compare the characteristics between the groups. Next, in order to assess the effect of the intervention among the different groups, a repeated measures design with time*group interaction effect will be chosen. A similar statistical approach will be performed for the secondary analyses.

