### Handling missing data

A great effort will be made to have complete data on outcome measures and to use all obtained information. For early drop-out within 4 weeks after starting the intervention, novel candidates will be foreseen.

For those who drop out in a later phase, efforts will be made to perform the end-of-study examination and if not feasible, these will be considered as missing data. In the case of missing data, some of the outcome measures (e.g. heart rate or blood pressure) can be retrieved through data from the HeartMan system, using the Last Observation Carried Forward (LOCF) principle.

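### Intervention patients who drop out within 4 weeks are replaced and left out of the analysis, and no post-use rating is described for them, so the user-experience result is at risk of upward bias

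*Protocol article*

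**What the plan says.** All references are to the Protocol article.

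- **What is measured, and in whom.** Secondary objectives lists an "Evaluation of the user experience of HeartMan to assess the expectations towards the system", and goes on to name the patients' experiences. It is "only measured in the intervention group), evaluated with the Unified Theory of Acceptance and Use of Technology questionnaire". Table 1 gives this questionnaire 37 items.
- **When.** Study objectives and outcome measures sets the general rule: "These measures are collected at start and end of the study, unless otherwise stated". No other time is stated for this questionnaire.
- **What the end visit is.** End-of-study visit says: "The intervention is terminated after using the system for three to six months". At that point "all participants from the intervention and control group undergo the end-of-study examination in the hospital", with the baseline questionnaires repeated.
- **Early drop-outs.** Handling missing data says: "For early drop-out within 4 weeks after starting the intervention, novel candidates will be foreseen". Baseline visit describes 24 reserve envelopes for this purpose, 12 per country.
- **Later drop-outs.** Handling missing data says: "For those who drop out in a later phase, efforts will be made to perform the end-of-study examination". Only if that is not feasible are the data treated as missing.
- **Analysis set.** Statistical analysis defines the main set for primary and secondary endpoints as "including all patients in the analysis who did not drop out within the first 4 weeks of the trial".

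**The concern.** Experience of a system can be rated only after using it. Under the stated schedule, that rating exists only at the end-of-study visit. A patient who leaves in week 2 because the wristband or the app is a burden is replaced and excluded from the main analysis. The effort to obtain an end examination is described only for those who leave later.

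For most endpoints, excluding early drop-outs is a general intention-to-treat problem. For acceptability it is more direct, because leaving early may be a sign of the very thing being measured. The analysis set is then selected on something close to the outcome. There is also no control-arm rating against which to see the loss, since only the intervention group answers.

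The Discussion shows why this result matters. It gives poor adherence to technology as one plausible reason for the mixed mHealth findings, says that smartphone-based interventions may be challenging for elderly patients, and expects the results to inform larger studies.

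**Working it through.** The plan gives no figure on this point, so there is none to reproduce. The check has two parts: following each type of patient through the stated rules, and an illustration of the possible size.

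**1. Who has a post-use rating under the stated rules**

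| Intervention patient | Replaced? | In main analysis? | Post-use rating |
|---|---|---|---|
| Completes the study | No | Yes | End-of-study visit |
| Stops using the system but stays in the trial | No | Yes | End-of-study visit, which covers all participants |
| Drops out after 4 weeks | No | Yes | Attempted; missing if not feasible |
| Drops out within 4 weeks | Yes | No | None described |

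Only the last row is a gap by design. Last observation carried forward does not fill it: the plan names it for measures retrievable from the system, such as heart rate or blood pressure. A carried-forward baseline questionnaire would record expectation, not experience.

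**2. Illustration of size**

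Inputs from the document:
- 80 intervention patients (Design).
- 24 reserve envelopes (Baseline visit).

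Assumptions:
- The reserves follow 1:2, giving 24 × 2/3 = 16 for the intervention arm. The same section calls the main series of 20 control and 40 experimental numbers balanced, which makes 1:2 a natural reading.
- Each of these replaces one intervention drop-out, and all 80 analysed patients give a rating.
- 80% of those analysed are favourable; between 20% and 80% of early leavers are.

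Replaced patients are additional to the 80, so with *e* of them the full denominator is 80 + *e*:

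- share without a rating = *e* / (80 + *e*)
- result over everyone = (80 × 0.80 + *e* × p) / (80 + *e*), where p is the favourable share among early leavers
- overstatement = 0.80 − result over everyone = [*e* / (80 + *e*)] × (0.80 − p)

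With *e* = 16, the share without a rating is 16/96 = 16.7%:

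| p | Result over all 96 | Overstatement (points) |
|---|---|---|
| 80% | 76.8/96 = 80.0% | 0 |
| 60% | 73.6/96 = 76.7% | 3.3 |
| 40% | 70.4/96 = 73.3% | 6.7 |
| 20% | 67.2/96 = 70.0% | 10.0 |

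With *e* = 4, the share is 4/84 = 4.8%. At p = 20% the result is 64.8/84 = 77.1%, an overstatement of 2.9 points; at p = 80% it is 0.

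**3. Does recovering later drop-outs close the gap?**

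Suppose also that 20 of the 80 drop out after 4 weeks (25%, assumed), that all leavers are 40% favourable, and that *e* = 16. The result over everyone is (60 × 0.80 + 36 × 0.40)/96 = 62.4/96 = 65.0%.

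- No later drop-out examined: 80.0% reported, overstatement 15.0 points.
- All later drop-outs examined: (48 + 8)/80 = 70.0% reported, overstatement 5.0 points.

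The early part therefore remains even with full recovery of the later drop-outs.

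**The case against.** A reader might infer that everyone who gives up on the system goes unrated and that replacements push the figure up. The documents do not support this, for three reasons.

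- Stopping use is not dropping out. All participants have an end-of-study examination, and low adherers stay in the main set: adherence of at least 50% defines a separate per-protocol analysis.
- Replacement and exclusion apply only within the first 4 weeks. For later drop-outs the plan tries to obtain the examination.
- Replacement does not itself shift the percentage. If 80% of stayers are favourable, adding more stayers leaves 80%. The distortion comes from the missing ratings.

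The direction is also not documented. The plan gives no reasons for drop-out, no expected early drop-out rate and no ratings. Patients in NYHA class 2–3 may leave because they are ill, and the bias is zero if leavers rate the system as stayers do. The Discussion also expects careful design, home visits and a help desk to make participation feasible for elderly patients.

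Finally, the root is the 4-week rule, which touches every endpoint, and this is only an additional secondary aim. Reasons for withdrawal and drop-out counts may well be recorded under the full protocol, and adherence is tracked separately.

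All of this stands as a limit on scope and size. It does not remove the core. Timing, replacement and analysis set are stated in the article, not left open, and together they leave early drop-outs without a described post-use rating.

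**Conclusion.** The point holds for intervention patients who drop out within 4 weeks. They are replaced, excluded from the main analysis, and have no described rating after use, on an outcome that early departure may itself reflect. The result is therefore at risk of upward bias; that it will be inflated is plausible but not shown.

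The size cannot be determined from the document. The illustration gives 0 to 10 points if all 16 assumed intervention reserves are used, and 0 to 2.9 points if 4 are. It rests on the assumed 1:2 split of the reserves and on assumed ratings, and zero is part of the range. Later drop-outs may add to the bias if their examination fails, but they are not missing by design.

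This is a secondary aim, and the remedy is cheap enough to be worth adopting. Ratings not taken at drop-out are hard to recover afterwards.

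**What to change.** For the user-experience objective only:

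1. Give the existing 37-item questionnaire at the time of drop-out to any intervention patient who has received the equipment, including within the first 4 weeks, by post or telephone if needed.
2. Analyse this objective over all intervention patients who received the equipment. Keep replaced patients in the denominator alongside their replacements.
3. Report the proportion who dropped out within 4 weeks next to the user-experience result.

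The cost is one existing questionnaire given earlier to the patients who leave, and a changed denominator. Allocation and sample size are unaffected. The downsides are some non-response among leavers, which should be shown, and a possibly less favourable figure.

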##### Sample size calculation

Sample size calculations were based on primary outcome data from the CHIRON project [13], showing that 90 patients are needed to show a difference of 5.8 beats per min in average daily awake heart rate– as a fundamental parameter correlating with HRQoL – with 90% power between the two groups. In order to account for possible drop-outs, the trial is performed enrolling 120 patients – 60 in each of the two participating countries – based on a 1:2 (control:intervention) randomization protocol.

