#### Primary objective

The primary endpoint is the self-reported improvement in self-care and HRQoL, measured by the Self-care of Heart Failure Index [20] and Minnesota Living with Heart Failure Questionnaire [21]

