### Intervention equipment

Participants randomized to the intervention group are equipped with a multi-monitoring health platform able to monitor, process and fuse physio-psychological and behavioural data. The main component of the trial equipment is the HeartMan wristband sensor developed by BITTIUM (Oulo, Finland). This is an ambulatory recorder and transmitter for heart rate, heart rate variability, galvanic skin response, skin temperature, respiration rate and motion. This wristband has Bluetooth communication, recording function, display, haptic interface and the ability to synchronize with other external devices. Apart from the HeartMan wristband sensor, the equipment consists of registered and commercially available devices including a digital bathroom scale (ADE, Model Silje BE1303), upper arm blood pressure monitor (A&D Medical, Model Number UA-611) and a pill box organizer (PuTwo, 7-Day AM/PM Night Reminder Medi-Planner). Furthermore, a smartphone (Nokia 6 TA_1021) with HeartMan app installed is provided for the duration of the trial.

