## Discussion

HeartMan aims to provide appropriate and comprehensive guidance on different domains of disease management in HF, tailored to the patient’s medical and psychological profile. This approach is intended to have a positive impact on HRQoL, which is the primary outcome of this trial.

The focus on HRQoL as a primary outcome instead of targeting hard outcomes such as mortality and hospitalization is one of the innovative approaches in comparison with previous mHealth studies. [8–10] HRQoL has gained more attention lately, often as a secondary outcome [11], although it also becomes more prominent as a primary outcome in recent studies [13].

Results on the effectiveness of mHealth technologies are rather mixed. Plausible reasons may be the focus on a single intervention modality (e.g. education) or a lack of patient’s adherence to technology. In HeartMan, the combination of different intervention modalities, adapted to the individual patient’s physical and psychological condition, is a unique approach, which makes HeartMan stand out from related projects. Another aspect that may increase the likelihood of successful adherence is the involvement of patients in the designing process of HeartMan, making it more adapted to the patient’s daily life.

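### The 90% power belongs to awake heart rate, which is neither the primary endpoint nor a listed outcome, so no power is stated for the primary question

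*Protocol article*

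**What the plan says.** The Sample size calculation section gives the trial's only power statement. It reports that "Sample size calculations were based on primary outcome data from the CHIRON project", that "90 patients are needed to show a difference of 5.8 beats per min in average daily awake heart rate", and that this holds "with 90% power between the two groups". Heart rate is justified "as a fundamental parameter correlating with HRQoL". Enrolment is raised to 120 for drop-out, with 1:2 allocation; the Design section gives 40 control and 80 intervention patients.

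The endpoint is defined elsewhere. Under Primary objective, "The primary endpoint is the self-reported improvement in self-care and HRQoL", measured by the SCHFI and the MLHFQ. The Statistical analysis section and the Discussion name HRQoL alone. Under Secondary objectives the only heart-rate outcomes are resting heart rate and heart rate during exercise, as measures of exercise tolerance.

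On equipment, "Participants randomized to the intervention group are equipped with a multi-monitoring health platform", whose main component is the wristband that records heart rate. The Baseline visit and End-of-study visit sections describe questionnaires and a six-minute walking test for both arms. The significance rule is that p "values < 0.05 will be considered to be statistically significant".

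**The concern.** Power is a property of one test on one variable: it depends on that variable's target difference and SD. The article gives a target difference for awake heart rate and none for the SCHFI or the MLHFQ. A correlation between two variables does not say how large a questionnaire effect goes with 5.8 beats per minute, nor that the two standardised effects are equal.

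The risk lies in interpretation. The article says the trial will show whether the technology can improve HRQoL. A reader who attaches the 90% to that question could take a non-significant MLHFQ result as good evidence against a worthwhile effect, when the design may have had clearly less than 90% power for an effect of moderate size.

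**Working it through.** **Inputs from the article:** difference 5.8 beats per minute; 90 patients needed; power 90%; alpha 0.05; allocation 1:2; 120 enrolled (40:80).

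**Assumptions:** two-sided test; normal approximation; equal SDs; loss in equal proportion in both arms. The SD of heart rate and the drop-out rate are not stated.

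**Step 1. The plan's own figure.** Without an SD, the 90 cannot be reproduced independently, but it can be inverted. The detectable standardised difference is

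d = (z for alpha + z for power) × √(1/n1 + 1/n2).

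For 30:60, d = (1.960 + 1.282) × √(1/30 + 1/60) = 3.242 × 0.2236 = 0.725. The implied SD is 5.8 / 0.725 = 8.0 beats per minute. So 90 patients at 1:2 is internally consistent with an SD of about 8. Enrolment also fits: 90 / 120 = 0.75, an implied loss of 25%.

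**Step 2. What the same design detects on any continuous outcome, in SD units.**

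| Completers | √(1/n1 + 1/n2) | 90% power (× 3.242) | 80% power (× 2.802) |
|---|---|---|---|
| 40:80 | 0.1936 | 0.63 SD | 0.54 SD |
| 30:60 | 0.2236 | 0.72 SD | 0.63 SD |

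**Step 3. Power at an assumed effect.** Power = Φ(d / √(1/n1 + 1/n2) − 1.960).

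- d = 0.5, 40:80: Φ(2.582 − 1.960) = Φ(0.622) = 73%.
- d = 0.5, 30:60: Φ(2.236 − 1.960) = Φ(0.276) = 61%.
- d = 0.3: 34% (40:80) and 27% (30:60).

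The 0.5 and 0.3 are illustrations; the article gives no expected questionnaire effect.

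**Step 4. Which SD.** The Statistical analysis section plans a repeated-measures model with a time-by-group interaction. With two time points this is a comparison of change scores, so the SD in Steps 2 and 3 is that of the change. It equals the single-visit SD times √(2(1 − r)), with r the correlation between baseline and end of study. At r = 0.5 the factor is 1.0, so the planned analysis gains nothing over a comparison of final scores.

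**Step 5. One primary or two.** The figures above use the full 5% for one questionnaire. If both are primary and alpha is split equally (0.025 each, an assumption), power at d = 0.5 falls to 63% (40:80) and 50% (30:60).

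**The case against.** The article is open about its basis: the sentence names heart rate and offers a reason for using it. It calls the trial a proof of concept and warns of preliminary results. No figure in the section is shown to be wrong. Losses may also be smaller than 25%: 24 extra randomisation envelopes are prepared, and patients who drop out within four weeks are to be replaced.

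Much of this stands. The point is not an arithmetic error, 30:60 is the pessimistic end of the range, and the 25% is only implied. But a trial that quotes 90% power and tests at 5% invites a confirmatory reading, and disclosing the variable does not give the primary test a power.

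Three stronger readings are tempting and are not supported:

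- **Awake heart rate is not measured in controls, so the powered comparison cannot be made.** No text says so. The section on study objectives and outcome measures says the listed outcomes are assessed in both groups, and only user experience is marked as limited to the intervention group. One listed outcome, daily activity, is itself measured with the wristband, so the text leaves open what controls wear. The flow chart is not shown. What can be said is that no means of recording awake heart rate in controls is described.
- **The 90 was derived for equal arms and is too small for 1:2.** The article does not give the allocation behind the 90, and an SD near 8 reproduces it at 1:2.
- **HRQoL power can be computed by scaling the heart-rate effect by a correlation.** No correlation is given. The scaling would also require the whole effect to run through heart rate, whereas the intervention has nutrition, exercise, medication and mental-support components.

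**Conclusion.** The point holds as a mismatch between the powered variable and the primary endpoint. The stated 90% refers to a variable that is neither primary nor listed as an outcome, and the asserted correlation does not transfer it. This follows from the text alone, whatever is or is not recorded in controls.

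The 90% would apply to a questionnaire only if its standardised effect were about 0.63 SD with no loss or 0.72 SD with 90 completers. At an assumed 0.5 SD, power is 61% to 73%. These figures rest on a two-sided 5% test, one primary questionnaire, no baseline adjustment, and the SD of the variable analysed. It would overstate the case to say that the trial can detect only large effects: with full completion it has 80% power for 0.54 SD.

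**What to change.** Keep 120 patients and rewrite the sample size paragraph:

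1. Say that the 90% refers to average daily awake heart rate only and is not the power of the primary test.
2. State what the 1:2 design can detect on the primary questionnaire or questionnaires. Suggested content: at two-sided 5% without baseline adjustment, 40:80 completers give 90% power for 0.63 SD and 80% for 0.54 SD; 30:60 completers (the 25% loss implied by 90 of 120) give 0.72 and 0.63 SD. Say that the SD is that of the change score under the planned time-by-group analysis, and convert to questionnaire points with a sourced SD.
3. Reconcile the Primary objective section (self-care and HRQoL) with the Statistical analysis section and Discussion (HRQoL alone), so that the figures apply to one named primary, or to two with a stated alpha for each.

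The cost is one paragraph and a decision on the primary endpoint, with no extra patients. The downside is that the stated figure becomes less favourable.
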